**Methods/design:**

The design of the study will be a multicenter prospective observational study of 400 patients who have sustained a humeral shaft fracture, AO type 12A or 12B. Treatment decision (*i.e.*, operative or non-operative) will be left to the discretion of the treating surgeon. Critical elements of treatment will be registered and outcome will be monitored at regular intervals over the subsequent 12 months. The primary outcome measure is the Disabilities of the Arm, Shoulder, and Hand score. Secondary outcome measures are the Constant score, pain level at both sides, range of motion of the elbow and shoulder joint at both sides, radiographic healing, rate of complications and (secondary) interventions, health-related quality of life (Short-Form 36 and EuroQol-5D), time to resumption of ADL/work, and cost-effectiveness. Data will be analyzed using univariate and multivariable analyses (including mixed effects regression analysis). The cost-effectiveness analysis will be performed from a societal perspective.

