## Methods/design

### Study design

The HUMMER trial will follow a multicenter, prospective observational trial design. Approximately 30 hospitals in The Netherlands will participate.

The decision to provide operative or non-operative treatment will be left to the discretion of the attending physician. We chose an observational design because a randomized controlled trial (RCT) would currently not be feasible. Many surgeons prefer not to participate in trials that involve randomization [21] and we know from experience that patients easily refuse to be randomized between operative and non-operative treatment. Inclusion problems were the main reason for failure of a previous RCT with the same research question as this study [20]. Well-designed and adequately reported observational studies are good alternatives to RCTs [22,23]. Preference of observational studies over RCTs in orthopedic trauma has been acknowledged [24,25]. They lead to similar outcomes without the limitations of randomization which may in practice decrease the validity of the outcomes [26,27]. These designs are increasingly used and accepted in surgical studies [28]. In order to answer our research question, we will make adjustments in the statistical analysis by using the propensity matching score method [29-32].

The trial is registered at the Netherlands Trial Register (NTR3617).

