### Sample size calculation

Calculation of the required sample size for the primary analysis is based on the assumption that the mean DASH in the non-operative group will be 16, with a Standard Deviation (SD) of 16 [8]. We expect less disability (*i.e.*, lower DASH score) at three months in the operative group; the expected DASH score in the operative group will be 10 (SD 10) [8]. A two-sided test with an α level of 0.05 and a β level of 0.2 requires 78 patients in every group. In order to account for loss of patients due to mortality (10%) and loss-to-FU (10% anticipated based upon previous studies by the research team), a sample size of 95 patients per group is needed.

Results of a retrospective study assessing clinical outcome of humeral shaft fractures, showed that 45-55% of all AO-subclasses were treated operatively [18]. In order to assess whether functional outcome scores differ between the fracture subtypes, a minimum of 2x20 patients per fracture subtype is sufficient. In order to achieve that, we need to include until at least 200 patients in both the operative groups and the non-operative group.

For the secondary analysis, some patients may be lost during the propensity score matching. Although we do not have a-priori data to determine how many patients will be lost, the 400 targeted patients will be more than sufficient.

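### The target of 400 patients is only the lowest total that could give 200 in each group, and it will rarely do so when surgeons choose the treatment

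*Protocol article*

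**What the plan says.** The section on sample size calculation derives 78 patients per group for the primary DASH comparison and raises this to 95 for mortality and loss to follow-up. It then moves to a larger number so that outcome can be compared between fracture subtypes. It holds that "a minimum of 2x20 patients per fracture subtype is sufficient" and concludes that "we need to include until at least 200 patients in both the operative groups and the non-operative group".

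The next paragraph of that section, on propensity matching, says that "the 400 targeted patients will be more than sufficient". The Methods/design part of the abstract describes a "multicenter prospective observational study of 400 patients". Neither place calls 400 a minimum.

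The study does not control the split. Under Study design: "The decision to provide operative or non-operative treatment will be left to the discretion of the attending physician". The Intervention section repeats this. For the expected split, the sample size section cites a retrospective study that "showed that 45-55% of all AO-subclasses were treated operatively". The Background, citing the same study, puts the operation rate at roughly half whatever the subclass.

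**The concern.** A per-group minimum and a total are interchangeable only when the allocation ratio is fixed. Here it is not, and the article describes no cap, quota or balancing step. Twice 200 is 400, but a total of 400 supplies 200 in both groups only at one exact split.

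The article therefore gives two end points for recruitment that will almost never coincide, and does not say which governs. If recruitment closes at 400, the smaller group will nearly always miss the number given as the basis for the subtype comparison. If it follows the per-group figure, the total in the abstract is too low and accrual runs longer than 400 patients would imply.

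**Working it through.** **Inputs.** From the sample size section: 200 per group, total 400, 45-55% operated across AO subclasses, DASH 16 (SD 16) versus 10 (SD 10), two-sided alpha 0.05, power 80%, 10% mortality and 10% loss to follow-up. From the Background: about 50% operated. From the Discussion: 10 patients per month. Assumption: treatment choices are independent with a common probability p of operation.

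**1. The plan's own primary figure.** n per group = (1.96 + 0.8416)² × (16² + 10²) / 6² = 77.6, rounded up to 78, as printed. For losses, 78 × 1.1 × 1.1 = 94.4 gives the printed 95; dividing instead, 78 / (0.9 × 0.9) = 96.3 gives 97. The difference is immaterial here.

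**2. Chance that 400 patients give at least 200 in both groups.** Let X be the number operated, X ~ Binomial(400, p). Both groups reach 200 only if X = 200, so the probability is C(400, 200) × p^200 × (1 − p)^200.

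**3. Expected smaller group at 400.** This is the mean of min(X, 400 − X) over the same distribution.

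**4. Expected total if recruitment runs until both groups hold 200.** This is the sum over n = 0, 1, 2, … of the probability that the condition is not yet met after n patients.

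| Share operated | P(200/200 at 400) | Expected smaller group at 400 | Expected total under per-group rule | Total for 90% chance of 200 in both |
|---|---|---|---|---|
| 50% | 4.0% | 192.0 | 415.9 | 434 |
| 47.5% or 52.5% | 2.4% | 188.3 | 424.4 | 449 |
| 45% or 55% | 0.5% | 179.8 | 444.8 | 475 |

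A hand check of step 4: at 50% the mean shortfall at 400 is 200 − 192.03 = 7.97, and filling it takes 7.97 / 0.5 = 15.9 further patients, giving 415.9. At 45%, 200 − 179.83 = 20.17 and 20.17 / 0.45 = 44.8, giving about 445.

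**5. Accrual.** 400 / 10 = 40 months. The per-group rule adds on average 16 / 10 = 1.6 months at 50% and 45 / 10 = 4.5 months at 45% or 55%.

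**6. Subtype counts.** The article gives no subtype distribution. If 200 per group is just enough for 20 in a subtype, the implied share is 20 / 200 = 10%; this is an assumption. The smaller group would then hold 0.10 × 192 = 19.2 such patients at 50%, or 0.10 × 180 = 18 at 45% or 55%, before any losses.

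**7. Primary comparison at 400 patients with 20% lost.** Power = Φ(6 / √(10²/n_op + 16²/n_non) − 1.96). With 144 operated and 176 not, it is 98.4%; with 160 and 160, 98.0%; with 176 and 144, 97.5%.

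**The case against.** The strongest reply is that there is no strict contradiction. The per-group wording is open-ended, 2 × 200 = 400 is correct, and 400 can be read as the floor or nominal value of that rule. Nothing in the article says that recruitment must stop at 400. This stands, and a reader who infers two logically incompatible rules goes too far: they agree at an exact 200/200 split. What remains is that the abstract and the sample size section present 400 as the study size without calling it a minimum. As an approximation to the per-group rule it errs in one direction only, since that rule cannot end below 400.

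A second reply is that the figures at 45% and 55% are edges of a range across subclasses, while the Background puts the rate near 50%. This also stands, so the 50% row should lead. Even there the chance of meeting the stated group size at 400 is only 4.0%.

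Third, the subtype consequence is thinly supported. The 10% share is back-calculated, and the article attaches no effect size or power to 20 per subtype and treatment, so no loss of power can be shown from having 18 or 19.

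A reader might also infer that a per-group quota biases the comparison because the end of recruitment depends on treatment choices. The document gives no mechanism for that: stopping on treatment counts uses no outcome data.

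**Conclusion.** The point holds as a small error in the stated sample size: 400 is the lowest total that could meet the per-group figure, and the article uses it as the study size. Over the article's own 45-55% range, 400 patients deliver 200 in both groups with probability 0.5% to 4.0%. The expected smaller group is about 180 to 192. Honouring the per-group figure takes about 416 to 445 patients on average.

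These results assume independent treatment choices and an overall operated share inside that range. Hospital-level preferences would change the probabilities, and a share outside the range would widen the gap; neither changes the fact that only an exact split reconciles the two figures. The values 180 and 192 are expectations: at 50% operated the smaller group still falls below 180 with about 4% probability, and at 45% or 55% with about 48%.

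It would be wrong to infer that the trial is underpowered for its main question. That comparison needs 95 per group and keeps about 97-98% power under the article's own assumptions. What is affected is the numerical basis for the subtype comparison and the accrual period.

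**What to change.** State one governing rule in the sample size section and align the other figure with it. Either of these would do:

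- **Total governs.** Recruitment stops at 400 whatever the split. Replace the per-group minimum with an expected smaller group of about 180-192, labelled as an expectation, and restate the subtype counts to match, giving the subtype shares they rest on.
- **Per-group minimum governs.** Recruitment runs until both groups hold 200. Restate the total, here and in the abstract, as at least 400, expected about 416-445.

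The first option needs no extra patients and makes the stated group size slightly less favourable. The second keeps the 200 per group at the price of an expected 16 to 45 extra patients, or about 1.6 to 4.5 months at the stated accrual rate. Because 416-445 is a range of averages, a sponsor choosing it may prefer to budget for the 90% figures of 434 to 475. Neither option changes the design or the primary analysis.

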### Statistical analysis

Data will be analyzed using the Statistical Package for the Social Sciences (SPSS) version 21 or higher (SPSS, Chicago, Ill., USA) and will be reported following the STrengthening the Reporting of OBservational studies in Epidemiology (STROBE) guidelines. Normality of continuous data will be assessed by inspecting the frequency distributions (histograms), and homogeneity of variances will be tested using the Levene’s test.

Descriptive analysis will be performed to report baseline characteristics (intrinsic variables and injury-related variables) and outcome measures for both treatment groups.

For continuous data mean and SD (parametric data) or medians and percentiles (non-parametric data) will be calculated and reported. For categorical data, numbers and frequencies will be calculated and reported for both treatment groups.

Univariate analysis will be performed in order to test the difference in the primary and secondary outcome measures between the operative and the non-operative group. Continuous data such as the DASH score at the different time points (primary outcome) will be tested using a Student’s T-test (parametric data) or a Mann Whitney U-test (non-parametric data). Chi-square analysis will be used for statistical testing of categorical data such as the nonunion rate. A p-value <0.05 will be taken as threshold of statistical significance.

For the primary analysis, a mixed linear regression model will be developed in order to model the relation between different covariates and the DASH score over time. Intrinsic and fracture-related variables that display a p-value <0.5 in univariate analyses will be added as covariate. Similar models will be developed for the Constant, SF-36, and EQ-5D score. Subgroup analysis (*e.g.*, elderly versus <65 years) will be performed.

For the secondary analysis we will develop a propensity score model as published before [43,44]. Characteristics including fracture type, age, gender, mechanism of injury, dominance, and activity levels will be included in this model; the resulting propensity score represents the chance of being operated. Next, the logit of the propensity score will be used in order to match each patient receiving operative treatment with one or more patients receiving non-operative treatment. The effect of operative treatment will be analyzed with linear or ordinal logistic mixed effects regression analysis taking the matched-pairs design into account. In the matched cohort, comparisons will be performed using a McNemar test (for categorical data), and a paired sample t test (parametric, continuous data) or a Wilcoxon signed rank test.

The economic evaluation will be performed from a societal perspective. Costs will be measured in accordance with Dutch guidelines for economic evaluations, using standard cost prices as published by Hakkaart-Van Rooijen et al. where possible [45]; effects will be discounted at a rate of 1.5% and costs at 4% per year [45]. The incremental cost-effectiveness ratio (ICER) of operative versus non-operative treatment will be expressed in a cost-utility ratio (*i.e.*, cost per QALY) using the EQ-5D utility score as effect measure. Uncertainty around this ratio will be presented using confidence ellipses on the cost-effectiveness plane and acceptability curves.

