### Outcome measures

The Disabilities of the Arm, Shoulder and Hand (DASH) outcome measure will serve as primary outcome measure. The DASH is a validated 30-item, self-report questionnaire designed to help describe the disability experienced by people with upper-limb disorders and also to monitor changes in symptoms and function over time [34,35]. It is scored in two components: the disability/symptom section (30 items, scored 1–5) and two optional Work and high performance Sport/Music modules (each 4 items, scored 1–5). The DASH disability/symptom score is a summation of the responses to 30 questions on a scale of 1 to 5, with an overall score ranging from 0 (no disability) to 100 (severe disability). At least 27 of the 30 items must be completed for a score to be calculated. The DASH optional modules aim to measure symptoms and function in athletes, performing artists and other workers whose jobs require a high degree of physical performance. These optional models are scored separately and each contains four items, scored 1–5. All items must be completed for a score to be calculated.

The secondary outcome measures are:

• Constant score

• Pain level at both sides (VAS)

• Range of Motion of the shoulder and elbow joint at both sides

• Rate of complications

• Rate of secondary interventions

• Time to resumption of work and other activities of daily living

• Health-related quality of life: SF-36 and EQ-5D

• Radiographic healing

• Cost of health care use and production loss

• Cost-effectiveness

The Constant score reflects both function and pain [36]. This scoring system consists of four variables that are used for assessing shoulder function. The right and left shoulder are assessed separately. The subjective variables are pain (15 points), activities of daily living (ADL; *i.e.*, sleep, work, recreation/sport; 10 points), and arm positioning (10 points), which give a total of 35 points. The objective variables are range of motion (ROM; 40 points) and strength (25 points), which give a total of 65 points. ROM includes forward flexion (10 points), lateral elevation (10 points), external rotation related to the head (10 points) and internal rotation related to the spine column (10 points). ROM will be measured with a goniometer. Strength of abduction will be measured using a calibrated spring balance.

Pain level will be determined using a 10-point Visual Analog Scale (VAS), in which 0 implies no pain and 10 implies the worst possible pain.

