## Discussion

The HUMMER trial will study outcome after operative versus non-operative treatment of humeral shaft fractures. Operative treatment is expected to result in earlier recovery than non-operative treatment. Earlier functional recovery will result in a better quality of life of patients, earlier work and ADL resumption, a higher level of independency, and less health care needs. Although costs for initial treatment will be higher in the operative group (due to surgery), we hypothesize that costs will be saved by less health care needs during the recovery process and less productivity loss. Despite higher initial costs, we expect that primary surgery will be more cost-effective. To the best of our knowledge, this is the first high-quality multicenter prospective observational study that will look at patient, medical and societal perspective in patients with a humeral shaft fracture.

Thirty hospitals in the Netherlands will participate. Inclusion of patients has started October 01, 2012 and the expectation is to include 10 patients per month. With a follow-up of one year the presentation of data will be expected in the beginning of 2016.

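### The general testing rule sends skewed costs to medians and rank tests, which do not answer whether mean cost per patient differs

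*Protocol article*

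**What the plan says.** In the protocol article, Outcome measures lists "Cost of health care use and production loss" as a secondary outcome. Cost-effectiveness is a separate item on the same list.

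Statistical analysis sets one univariate rule for every outcome: "Univariate analysis will be performed in order to test the difference in the primary and secondary outcome measures". The branch is chosen by eye: "Normality of continuous data will be assessed by inspecting the frequency distributions (histograms". Non-normal data are summarised so that "medians and percentiles (non-parametric data) will be calculated and reported", and are tested with a Student's t-test "or a Mann Whitney U-test (non-parametric data"), with 0.05 as the threshold. In the propensity-matched cohort the same split becomes a paired t-test or a Wilcoxon signed-rank test. No outcome is exempted.

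The economic paragraph of the same section covers unit prices, discounting, the incremental cost per QALY, confidence ellipses and acceptability curves. It names no separate comparison of costs and does not take costs out of the univariate rule.

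The Discussion states the cost hypothesis. Initial treatment is expected to cost more in the operative group, but "we hypothesize that costs will be saved by less health care needs during the recovery process and less productivity loss".

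**The concern.** Cost and production-loss data are usually right-skewed, so the histogram check would normally send them to medians and Mann-Whitney. The hypothesis is about total cost over the year, and therefore about the mean per patient. Medians do not add up to a total. Mann-Whitney responds to whether a patient from one group tends to cost more than a patient from the other, which matches a comparison of means only when the two distributions share a shape.

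The documents give reason to expect different shapes. Nearly every operated patient carries the cost of surgery. Both groups also have a minority with non-union: Background gives 15-30% after operative and 2-23% after non-operative treatment, and says most of the latter need secondary surgery.

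At stake is the cost result itself. A significant cost p-value, with medians beside it, could point the opposite way to the mean cost difference behind the cost-per-QALY ratio in the same report.

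**Working it through.** **Inputs.** From the documents: at least 200 patients per group and losses of 10% mortality plus 10% follow-up (Sample size calculation), so 200 × (1 − 0.20) = 160 evaluable per group; the two non-union ranges in Background; two-sided 0.05. The documents give no cost figure, so there is none to reproduce and all cost inputs below are assumptions.

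**Step 1: the mechanism, in closed form.** Take lognormal costs with mean 10,000 in both groups, log-SD 0.8 in one (A) and 1.0 in the other (B).

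- Median = mean × exp(−s²/2). A: 10,000 × exp(−0.32) = 7,261. B: 10,000 × exp(−0.50) = 6,065.
- P(A > B) = Φ[((s_B² − s_A²)/2) / √(s_A² + s_B²)] = Φ[0.18 / √1.64] = Φ(0.141) = 0.556.

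Mann-Whitney tests against 0.5, so it tends to call A dearer although the means are equal. Simulated at 200 per group (4,000 trials), it rejects in 49% and Welch's t-test in 4.8%. The signed-rank test on 200 pairs rejects in 22%. With log-SD 1.0 in both groups, Mann-Whitney rejects in 5.1%. Swapping the labels of A and B reverses the direction, so the sign depends only on which group is assumed more skewed.

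**Step 2: non-union in both groups.** Routine non-operative cost is gamma with mean 1 and CV 0.5 to 1.0. Non-union, with probability q_N or q_O, adds a cost of mean F = 1.5 or 3. Operative routine CV is 0.8 times the non-operative one. Equal total means require

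operative routine mean = 1 + q_N·F − q_O·F.

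Results at 160 per group, 500 trials per scenario:

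| q_N / q_O | F | CV | Operative routine mean | Mann-Whitney rejections |
|---|---|---|---|---|
| 15/15, 20/20, 23/23% | 1.5 or 3 | 0.5-1.0 | 1.00 | about 5-16% |
| 10/15% | 1.5 or 3 | 0.5-1.0 | 0.925 or 0.85 | operative dearer 0-15%, cheaper 0-24% |
| 10/20% | 3 | 0.5 | 0.70 | 79%, operative cheaper |
| 2/15% | 3 | 0.5 | 0.61 | nearly 100%, operative cheaper |
| 23/15% | 1.5 or 3 | 0.5-1.0 | 1.12 or 1.24 | 12-45%, operative dearer |

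**Step 3: an explicit surgery cost as well.** Add S = 0.3 or 0.6 to every operated patient, with CV 0.8 or 1.5, q_N = 2, 10 or 23% and q_O = 15 or 30%. The operative routine mean is then 1 + q_N·F − S − q_O·F. Of the 2 × 2 × 2 × 3 × 2 = 48 combinations, 38 leave a workable routine cost. Mann-Whitney rejects in 6% to over 99% of trials and exceeds 10% in 33 of the 38. Most rejections call operative care dearer, but in a handful of scenarios they lean the other way (up to 72%). Welch's test rejects in 4-6%.

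**Overall**, with both tails in the model, Mann-Whitney rejects in about 3% to nearly 100% of trials at equal means, in either direction. Welch's test rejects in about 3-8%.

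**The case against.** **Means are already analysed.** A cost-per-QALY ratio with confidence ellipses needs the mean cost difference and its uncertainty, and the Discussion moves straight from saved costs to cost-effectiveness. This stands in part: the ratio is sound and the point does not touch it. But costs are listed as a separate outcome, and the only stated comparison for that outcome is the univariate rule.

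**Application to costs is inferred.** The rule's examples are the DASH score and non-union, the article is condensed, and the branch depends on a histogram not yet drawn. The dependence on the histogram is a real condition. But the rule as written covers all secondary outcomes without exception, so this is a stated rule that fits one outcome badly, not a detail left to a fuller document.

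**Direction and size.** A reader might infer that Mann-Whitney will wrongly call operative care dearer, even when its mean cost is lower. That follows if only the non-operative group has an expensive tail: with 10% non-union there and none after surgery, the Step 2 model gives 21-92% rejections, all in that direction. The documents do not support this. The same Background sentence gives 15-30% non-union after operative treatment, and once that is included the direction can reverse and the size can fall to near nominal.

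**Conclusion.** The point holds as a mismatch between the stated rule and the cost question. If costs are judged non-normal, they are summarised by medians and tested by a method that does not control error for mean cost unless the two groups' distributions share a shape. Neither a direction nor a single size can be claimed. At equal means the rejection rate runs from about 3% to nearly 100%, depending wholly on assumed costs, against about 3-8% for a test of means and 5% for Mann-Whitney under identical shapes.

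The effect is confined to one secondary outcome, in the unadjusted and matched comparisons. It would be wrong to infer that the cost-per-QALY result is biased by this rule. The harm is a cost p-value and medians that may disagree with that result without the reader being able to see why.

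**What to change.** In Statistical analysis, exempt costs of health care and production loss from the t-test/Mann-Whitney choice and from median-only reporting, and from the signed-rank option in the matched cohort. Report arithmetic mean cost per group and the mean difference with a bootstrap 95% confidence interval, resampling patients in the full cohort and matched sets in the propensity cohort. Keep this difference consistent with the cost difference used in the cost-per-QALY ratio. Medians and percentiles may stay as description.

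This takes a sentence or two and no new data, and the bootstrap also suits the planned acceptability curves. The price is wider intervals when costs are heavily skewed. The change does not deal with confounding in the unadjusted comparison, which affects means and ranks alike.

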The range of motion (ROM) of the shoulder (*i.e.*, abduction and forward flexion) and the elbow joint (*i.e.*, flexion and extension) will be measured using a goniometer. Both sides will be assessed separately, and the loss of ROM will be calculated.

Complications will be recorded from medical charts. Complications may include: 1) surgical site infection; 2) wound dehiscence; 3) skin problems (*e.g.*, skin at risk, skin necrosis); 4) dystrophia; 5) radial nerve palsy; 6) malunion; 7) implant failure (screw breakout); 8) cuff pathology; 9) secondary fracture dislocation; or 10) non-union. Non-union is defined as a failure to heal at twenty-six weeks post fracture with no progress towards healing seen on the most recent radiographs [37].

Secondary intervention within one year of initial treatment to promote fracture healing, relieve pain, treat infection, or improve function will be recorded from medical charts. Interventions will be categorized as: 1) osteosynthesis with or without bone grafting; 2) implant exchange with or without bone grafting; 3) implant removal; 4) incision and drainage for superficial surgical site infection; or 5) incision and drainage for deep surgical site infection. The indication and admission duration for all intervention will also be recorded.

Presence of radiographic healing will be determined using X-rays. Fracture consolidation is defined when one of the three criteria listed is present; 1) bridging of fracture by callus/bone trabeculae or osseous bone; 2) obliteration of fracture line/cortical continuity; or 3) bridging of fracture at three out of four cortices.

The time to resumption of work and activities of daily living will be recorded using a custom-made questionnaire.

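### For time to resumption of work and daily activities, the protocol names only methods that ignore censoring and does not say how patients without an observed time are counted

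*Protocol article*

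**What the plan says.** The Outcome measures section lists "Time to resumption of work and other activities of daily living" among the secondary outcomes and adds: "The time to resumption of work and activities of daily living will be recorded using a custom-made questionnaire". Table 1 in Study procedures collects it at every visit from two weeks to 12 months, with visits counted from the start of treatment.

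The Statistical analysis section sets the scope of testing: "Univariate analysis will be performed in order to test the difference in the primary and secondary outcome measures". It then names two families of test. Continuous data, with the DASH as the example, "will be tested using a Student’s T-test (parametric data) or a Mann Whitney U-test (non-parametric data"). For the rest, "Chi-square analysis will be used for statistical testing of categorical data such as the nonunion rate".

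Beyond these tests, a mixed linear model is planned for the DASH, and "Similar models will be developed for the Constant, SF-36, and EQ-5D score". Time to resumption is not in that list. For the matched cohort, "The effect of operative treatment will be analyzed with linear or ordinal logistic mixed effects regression analysis", with McNemar, paired t and Wilcoxon signed rank tests alongside.

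The Sample size calculation allows for "loss of patients due to mortality (10%) and loss-to-FU", the latter also at 10%.

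Kaplan-Meier curves, the log-rank test, Cox regression, censoring and competing risks are not mentioned anywhere in the article.

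**The concern.** Time to resumption is a time-to-event outcome. A patient who has not resumed by 12 months, or who dies or is lost before resuming, has no observed time. What is known is only that resumption had not happened by a certain date. The tests and models named for the secondary outcomes cannot use that information as it stands: the patient must either be given an invented value or be left out.

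Leaving such patients out conditions the comparison on a good outcome and removes more patients from the slower group, so the contrast can shrink. In a paired test on the matched cohort, one missing time also removes its partner.

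The outcome bears on what the study expects to show. The Abstract's main hypothesis is faster recovery after operation, and the Discussion predicts earlier return to work and daily activities.

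**Working it through.** **The plan's own figures.** No figure is stated for time to resumption. The DASH sample size is the only related calculation, and it reproduces: n per group = (16² + 10²) × (1.960 + 0.842)² / 6² = 77.6, rounded up to 78; 78 × 1.1 × 1.1 = 94.4, rounded up to 95. It is not affected by this point.

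**How many times may be incomplete.** With 200 per group and the stated 10% mortality and 10% loss, 200 × 0.8 = 160 to 200 × 0.9 × 0.9 = 162 have complete follow-up. Up to 38 to 40 per group could therefore have incomplete follow-up, before counting those followed to 12 months who never resume. This is an upper bound on incomplete resumption times from deaths and losses, because a patient who resumes and later dies or is lost still has a time.

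**Check 1: medians among those who resumed.** Assumptions: exponential times with true median m weeks, cut at 52 weeks, no other losses, and a ratio of medians of 1.5.
- Proportion resumed by week 52: F = 1 − exp(−52 ln 2 / m).
- Median among resumers: −ln(1 − F/2) × m / ln 2.

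For m = 20, F = 0.835 and the median among resumers is 15.6. For m = 30, F = 0.699 and the median is 18.6. The true difference of 10 weeks becomes 3.0, so 30% is kept. The range:

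| True medians (weeks) | Medians among resumers | Share of difference kept |
|---|---|---|
| 6 v 9 | 6.0 v 8.8 | 93% |
| 8 v 12 | 7.9 v 11.2 | 82% |
| 10 v 15 | 9.6 v 13.1 | 70% |
| 20 v 30 | 15.6 v 18.6 | 30% |

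The loss is small when nearly everyone resumes within the year and large when many do not.

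**Check 2: a difference in non-resumption.** Simulation of 500 trials per scenario with 200 per group. Assumptions: median 10 weeks in both groups among those who resume, 5% never resuming in the operative group, 20% lost at a uniformly distributed time unrelated to recovery, and cut-off at 52 weeks.

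| Never resume, non-operative | Resumers only, t-test or Mann-Whitney: rejects | Log-rank, all patients: rejects |
|---|---|---|
| 10% | about 4-5% | 25% |
| 15% | about 5% | 64% |
| 20% | about 4-5% | 91% |
| 25% | about 4% | more than 99% |

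At 15%, the resumers-only analysis excludes about 12% v 21% of patients, and both groups show the same median among resumers (9.1 weeks). If non-operative resumers are also slower (median 13 v 10 weeks, 15% v 5% never resuming), rejection is 41% for the t-test, 37% for Mann-Whitney and 98% for log-rank.

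**Check 3: other uses of the named tests.** With 5% v 15% never resuming, equal times otherwise and 160 per group, Mann-Whitney on resumers only rejects in about 5% of trials. Mann-Whitney with non-resumers ranked last rejects in about 35%, and chi-square on ever resumed, yes or no, in about 86%. How much is lost therefore depends on how non-resumers are counted, which the article does not state.

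**The case against.** A reader might infer that the plan forces time to resumption into a t-test or Mann-Whitney test and drops everyone who has not resumed. The article does not say so. It never classifies this outcome, its example of continuous data is the DASH, and no sentence excludes non-resumers. Chi-square on resumed yes or no at a visit is open under the stated plan, and a Mann-Whitney test could rank non-resumers last. Check 3 shows that both can detect what a resumers-only comparison misses. It can also be argued that the coding of such patients is a matter for a full protocol or analysis plan that is not shown.

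Further, the size rests on assumed rates. The article expects mean DASH scores of only 10 v 16 at three months. That does not fix resumption times, but short medians are at least as plausible as long ones, and with short medians little is lost. The 10% + 10% losses were set for the DASH. The primary objective is the DASH, and production loss has its own questionnaire items, so neither depends on this test.

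Most of this stands as a limit on the point and does not remove it. The article does not simply leave the method open: it says its univariate tests cover the secondary outcomes and names the tests. Neither workaround is stated. Chi-square by visit discards the timing and cannot place patients lost before that visit. Ranking non-resumers last still needs a rule for deaths and losses.

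**Conclusion.** The point holds in a limited form. For a secondary time-to-event outcome followed to 12 months, the article names only tests and models that ignore censoring, in both the full and the matched cohort, and does not say how patients who have not resumed, have died or are lost are counted. If only observed times are compared, the test selects on good outcome and can understate a difference between treatments.

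The documents do not fix how large that would be. Under exponential times with a 1.5-fold ratio of medians and a 52-week cut, between about 93% (6 v 9 weeks) and about 30% (20 v 30 weeks) of the difference in medians is kept. If the groups differ only in the share who never resume, a resumers-only test has no power beyond its false-positive rate. The documents support neither the claim that such patients will be dropped nor any single figure for the loss.

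**What to change.** In the Statistical analysis section, state that resumption of work and resumption of daily activities are each analysed as time-to-event outcomes:
- One stated time origin, consistent with Study procedures, which counts visits from the start of treatment.
- Kaplan-Meier or cumulative incidence curves by treatment, with death as a competing event and censoring at last contact or 12 months.
- A Cox or cause-specific hazard model adjusted for confounders named in advance. The variables listed for the propensity score are a natural choice. The primary mixed model offers no fixed set to borrow, because its covariates are chosen by a univariate p-value below 0.5.
- A version for the matched cohort that accounts for the matching.

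The cost is a little more analysis work and a change of wording. The resumption data are already scheduled at every visit, so no new data collection is needed, and the sample size does not change.
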